## Abstract

**Abstract:**

**Introduction:**

Fast and accurate diagnosis of acute stroke is crucial to timely initiate reperfusion therapies. Conventional high-field (HF) MRI yields the highest accuracy in discriminating early ischaemia from haemorrhages and mimics. Rapid access to HF-MRI is often limited by contraindications or unavailability. Low-field (LF) MRI (<0.5T) can detect several types of brain injury, including ischaemic and haemorrhagic stroke. Implementing LF-MRI in acute stroke care may offer several advantages, including extended applicability, increased safety, faster administration, reduced staffing and costs. This multicentric prospective open-label trial aims to evaluate the diagnostic accuracy of LF-MRI, as a tool to guide treatment decision in acute stroke.

**Methods and analysis:**

Consecutive patients accessing the emergency department with suspected stroke dispatch will be recruited at three Italian study units: Azienda Sanitaria Locale (ASL) Abruzzo 1 and 2, Istituto di Ricerca e Cura a Carattere Scientifico (IRCCS) Humanitas Research Hospital. The estimated sample size is 300 patients. Anonymised clinical and LF-MRI data, along with conventional neuroimaging data, will be independently assessed by two external units: Marche Polytechnic University and ‘G. Martino’ Polyclinic University Hospital. Both units will independently adjudicate the best treatment option, while the latter will provide historical HF-MRI data to develop artificial intelligence algorithms for LF-MRI images interpretation (Free University of Bozen-Bolzano). Agreement with conventional neuroimaging will be evaluated at different time points: hyperacute, acute (24 hours), subacute (72 hours), at discharge and chronic (4 weeks). Further investigations will include feasibility study to develop a mobile stroke unit equipped with LF-MRI and cost-effectiveness analysis. This trial will provide necessary data to validate the use of LF-MRI in acute stroke care.

**Ethics and dissemination:**

The study was approved by the Research Ethics Committee of the Abruzzo Region (CEtRA) on 11 May 2023 (approval code: richyvgrg). Results will be disseminated in peer-reviewed journals and presented in academic conferences.

**Trial registration number:**

NCT05816213; Pre-Results.

STRENGTHS AND LIMITATIONS OF THIS STUDYThis is the first study evaluating the diagnostic accuracy of low-field (LF) MRI in acute stroke care, as a tool to guide treatment decisions.The multicentric design will allow to investigate the diagnostic performance of LF-MRI both on site and independently by external units.The performance of LF-MRI will be evaluated at different time points, providing information on the evolution of stroke lesions over time (24 hours to 4 weeks).Further investigations will include cost-effectiveness analysis and feasibility study to develop an ambulance equipped with LF-MRI.Study limitations include its non-randomised design, although clinical and LF-MRI data will be compared with conventional neuroimaging findings in a blinded fashion.

## Introduction

 Stroke is the second-leading cause of mortality and morbidity worldwide, resulting in more than 5.5 deaths and over 110 million disability-adjusted life-years lost per year.^1^ The annual incidence rates in the Italian population ranges from 175:100 000 to 360:100 000 in men and from 130:100 000 to 273:100 000 in women.^2^ Stroke can be broadly classified into ischaemic and haemorrhagic, the latter of which include intracerebral and subarachnoid haemorrhage. Ischaemic stroke refers to an infarction of the brain, spinal cord or retina and accounts for ~71% of all strokes globally.^3^ Advances in brain imaging identified that much of the initial clinical deficit in patients with stroke is related to a hypoperfused non-functional part of the brain termed ischaemic penumbra. This region progressively evolves to irreversibly injured tissue over time (ischaemic core).^3^ However, rapid reperfusion can salvage the ischaemic penumbra leading to restoration of normal function. This discovery formed the rationale for reperfusion therapies, which are strictly time dependent. Intravenous thrombolysis (IVT) can reduce the disability when administrated within 4.5 hours of stroke onset (defined as the time from when the patient was last known to be healthy), although selected patients with favourable brain perfusion imaging may benefit up to 9 hours.^4^ Endovascular thrombectomy (EVT) reduces disability in patients with cerebral large vessel occlusion (LVO) through the mechanical retrieval of the clot via catheter angiography. EVT must be performed within 6 hours of the time the patient with a stroke was last to known to be healthy and, in patients selected using brain perfusion imaging, up to 24 hours.^5^ The outcome of both IVT and EVT relies on the accuracy of diagnosis and on the time from symptoms onset to treatment start—the faster the better. Therefore, improving diagnostic accuracy and accelerating treatment initiation remain the key challenges for health systems to maximising benefits of reperfusion.

Accurate stroke diagnosis involves distinguishing between ischaemic lesions and intracerebral haemorrhage (ICH), a critical step in assessing patients’ eligibility for IVT. Additionally, ischaemic stroke must be differentiated from common mimics (eg, migraine, seizures, metabolic and functional disorders). Neuroimaging of acute stroke usually involves brain CT, which shows excellent accuracy in detecting ICH (~100%).^6^ However, high-field (HF) MRI currently yields the highest sensitivity and specificity in detecting acute ischaemic lesions. Specifically, diffusion-weighted imaging (DWI) becomes abnormal within few minutes of ischaemic stroke and has shown 86%–100% specificity and 73%–92% sensitivity (98% accuracy) in detecting early ischaemic lesions.^7^ Over the next hours, further ischaemic injury leads to vasogenic oedema, which is visible on fluid-attenuated inversion recovery (FLAIR) sequences. FLAIR offers a sensitivity of 90% in the acute phase and 88% in the subacute phase in detecting brain ischaemic changes.^8^

Advanced brain imaging modalities such as perfusion CT and perfusion-diffusion MRI can identify salvageable brain tissue, potentially extending the time window for reperfusion. Indeed, patients with viable brain tissue at CT perfusion or perfusion-diffusion MRI can benefit from IVT administered up to 9 hours of ischaemic stroke onset,^4^ and from EVT performed up to 24 hours (in patients with anterior circulation LVO).^9^ Additionally, MRI-guided IVT has been shown to significantly improve the functional outcome of patients with stroke of unknown onset who have an ischaemic lesion visible on DWI but no parenchymal hyperintensity on FLAIR.^10^

Despite these advantages, rapid access to HF-MRI is often limited by the presence of contraindications or by its unavailability, especially in small hospitals and at night.^3^ Indeed, installing 1.5T or 3T MRI scanners is expensive and very demanding for the infrastructure and it requires continuous maintenance, sophisticated siting and utilisation. A low-field (LF) MRI scanner could operate in a broader range of environments, such as the emergency department (ED) or the ambulance setting (mobile stroke unit, MSU). Very recently portable LF-MRI has been evaluated in critically ill patients and resulted able to detect several types of brain injury, including ischaemic stroke, ICH, subarachnoid haemorrhage, traumatic brain injury and brain tumours.^11^ A preliminary study conducted in the intensive care unit setting demonstrated also an acceptable mean examination time (about 35 min) to deliver a complete protocol of diagnostic-grade sequences (T1W, T2W, T2, FLAIR, DWI).^12^ As for ischaemic stroke, performing DWI at 64 mT (Hyperfine LF-MRI, Guilford, Connecticut, USA) has been shown to successfully identify early lesions.^11^,^13^ Furthermore, LF-MRI DWI and FLAIR sequences were able to detect infarcts as small as 4 mm in diameter in >90% patients across cortical, subcortical and cerebellar structures, showing a strong correlation between ischaemic volumes, stroke severity and functional outcomes at the discharge.^14^

Referring to ICH, LF-MRI was evaluated mostly in the subacute phase, therefore, data on the hyperacute assessment are largely missing.^15^ Interrater discordance among expert neuroradiologists was observed mainly in detecting small haematomas, especially located in the posterior fossa.^15^ Potential advantages and current limitation of LF-MRI in acute stroke are reported in box 1.

Box 1Applicability of low-field (LF) MRI in acute stroke: advantages and limitationsPotential advantagesLF-MRI provides point-of-care service to stroke patients.Well-maintained site, sophisticated setting and utilisation are not strictly necessary.The scanning protocol of LF-MRI is simpler compared with conventional high field (HF) MRI, thus potentially reducing the time of images acquisition.LF-MRI technology is compatible with nearby ferromagnetic materials and enables scanning outside the traditional MR suite. It is not necessary to remove vital sign monitors, intravenous infusion pumps or ventilators.LF-MRI allows easy patients handling and positioning and extends advanced neuroimaging applicability to complex patients (eg, critically ill patients, patients with agitation, accidental or implanted ferromagnetic devices such as pacemakers).Reduced staffing through easy data acquisition with automated stroke sequences (machine learning approach).Reduced patients transfer to different services, thus hampering risks associated with critical or complex patient mobilisation and probability of in-hospital infections.LF-MRI associated with an equipped van potentially may enable to diagnose and characterise acute stroke patients even in remote area or large city outskirts.Lower costs versus HF MRI.
Limitations
No conclusive data are available on LF-MRI diagnostic accuracy, sensitivity and specificity in the acute stroke setting.Not known impact of implementing LF-MRI on door-to-needle time and time to intravenous thrombolysis initiation.Accuracy of LF-MRI in discriminating intracerebral haemorrhage from ischaemic stroke lesions must be improved to reach 100%, especially for small and subtentorial bleeds.Accurate identification of the infarct core and assessment of collateral flow must be implemented for guiding correct treatment choice.Integration between LF-MRI and tissue plasminogen activator administration for thrombolysis monitoring is still to be tested.LF-MRI was never investigated as a tool to guide treatment decisions in acute stroke care.No information is available on LF-MRI performance in assessing the evolution of ischaemic/haemorrhagic lesions over the chronic phase.Currently, only predetermined LF-MRI sequences are administrable, so that protocols that are more targeted on acute stroke need to be further developed and tested (eg, perfusion study, angiographic sequences).LF-MRI mobile stroke units have not been designed and validated in real clinical settings.

Here, we designed a multicentric open-label prospective trial to evaluate a point-of-care LF-MRI system in the diagnosis of acute stroke and in guiding treatment decisions.

## Methods and analysis

### Objectives

The objectives of the present study are the following: (1) To assess the diagnostic yield of LF-MRI for the diagnosis of acute stroke as compared with conventional neuroimaging (CT and HF-MRI). (2) To evaluate the performance of LF-MRI as a tool to guide treatment decisions in acute ischaemic stroke. This study will further develop LF-MRI technology and integrate it with artificial intelligence (AI) to facilitate interpretation of imaging findings. Further investigations of the present study include feasibility assessment of MSU equipped with LF-MRI and cost-effectiveness analysis of LF-MRI implementation in the acute stroke care.

### Study design

The Point-of-care low-field MRI in acute Stroke study is a multicentric, prospective clinical trial involving adult patients with suspected stroke. Recruitment of patients will be performed at three study units: Azienda Sanitaria Locale (ASL) Abruzzo 1, Hospitals of L’Aquila and Avezzano, Italy (ASLAQ); ASL Abruzzo 2, Hospital of Chieti, Italy (ASLCH); Istituto di Ricerca e Cura a Carattere Scientifico (IRCCS) Humanitas Research Hospital of Milan, Italy (HUM). Additional units contributing to the study will include:

University of L’Aquila (UNIVAQ) will be in charge of study coordination, data analysis and management, optimisation of LF-MRI protocols, and cost-effectiveness assessment of LF-MRI within the Italian public care system.Marche Polytechnic University (UNIPM) will perform independent assessment and adjudication of anonymised clinical, LF-MRI and conventional neuroimaging data in a blinded fashion; it will also identify the best possible treatment option for patients with suspected ischaemic stroke (IVT, EVT, combined revascularisation treatment, no revascularisation).‘G. Martino’ Polyclinic University Hospital (POLIME) will perform blinded and independent assessment and adjudication of anonymised clinical and conventional neuroimaging data, also will identify the best possible treatment option for patients with suspected ischaemic stroke and provide historical HF-MRI data of patients with stroke to be used for AI algorithms training.Free University of Bozen-Bolzano (UNIBZ) will develop and optimise AI algorithms suitable for LF-MRI images interpretation starting from anonymised conventional HF-MRI and LF-MRI data provided by ASLAQ, ASLCH, HUM and POLIME.University of Cassino and Southern Lazio (UNICAS) will perform a feasibility study to develop an ambulance (MSU) equipped with an LF-MRI scanner.

Agreement with conventional neuroimaging will be evaluated at different time points (hyperacute, acute—24 hours, subacute—72 hours, discharge, chronic—4 weeks) by ASLAQ, ASLCH, HUM, POLIPM and POLIME. At each time point, LF-MRI will be scheduled immediately after conventional neuroimaging to ensure comparability between performed investigations. In summary, this trial will provide necessary data to validate the use of LF-MRI in the acute stroke healthcare system.

Patients with suspected acute stroke will undergo diagnostic procedures and management according to usual clinical care. LF-MRI will be performed on admission, 24 hours, 72 hours, at the hospital discharge and 4 weeks after the event. LF-MRI findings will not be used to make clinical decisions on patients’ management. Every time a stroke dispatch is activated, the dedicated research staff will be alerted by the local neurologist on duty. The research staff will check eligibility criteria, obtain informed consent and perform study procedures independently of the personnel in charge of managing the acute stroke case. All included patients with suspected stroke will be managed and treated per usual care by the hospital staff not involved in study procedures. Conventional stroke imaging will be performed as needed according to current clinical practice (non-contrast CT+CT angiography and/or HF-MRI+MRI angiography in selected cases, with/without CT or HF-MRI perfusion study).

For the aim of the study, all included patients will be investigated with LF-MRI at predefined time points (24 hours, 72 hours, hospital discharge, 4 weeks). The acquisition of LF-MRI will be performed by a dedicated study staff that will be distinct from the clinical staff involved in the care of the acute stroke patient, thus not subtracting time or resources to usual care. Information obtained by LF-MRI will not be used to take clinical decisions regarding further investigations or treatment. Due to feasibility reasons, the study will include only patients presenting to the ED with suspected stroke during weekdays daytime hours. Study procedures are summarised in figure 1.

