### Time points and collected variables

The following clinical variables will be collected at the specified time point:

Hyperacute (ED): demographical data, time from symptom onset (precise onset, unwitnessed, wake-up stroke), onset-to-door-time, door-to-imaging time, clinical severity (National Institute of Health Stroke Scale, NIHSS), type of neuroimaging, duration of LF-MRI scanning, conventional neuroimaging and LF-MRI findings (detection of ischaemic or haemorrhagic lesion(s), lesion(s) number, location and volume, detection and characteristics of possible LVO, collateral flow assessment, Alberta Stroke Programme early CT score^16^ and/or DWI/FLAIR mismatch for MR, pre-EVT grade of perfusion according to the thrombolysis in cerebral infarction—TICI—scale), treatment decision (IVT, EVT, IVT+EVT, none), time (door-to-needle for IVT and door-to-groin for EVT), clinical outcome (NIHSS score immediately after IVT/EVT—if performed) and reperfusion outcome (TICI score immediately after EVT—if performed).Acute (24 hours) and subacute (72 hours): clinical severity (NIHSS), conventional neuroimaging type and findings, LF-MRI findings (lesion volume and characteristics, evolution—for example, presence and entity of haemorrhagic transformation).Hospital discharge: days of hospital stay, functional outcome at discharge (modified Rankin scale), final adjudication of the event (ischaemic stroke, ICH, SAH or mimic), assessment of aetiology according to the Trial of ORG 10172 in Acute Stroke Treatment (TOAST) classification^17^—for ischaemic stroke.Chronic (4 weeks): conventional neuroimaging type and findings, LF-MRI findings (lesion volume, characteristics and evolution), assessment of stroke aetiology (TOAST)^17^ also considering findings from postdischarge clinical investigations.

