### Sample size calculation

The sample size of this study has been calculated considering the sensitivity and specificity of conventional HF-MRI (91%–100% and 86%–100%, respectively), available data on LF-MRI diagnostic performance (∼90% sensibility and ∼80% specificity),^11^,^13^ as well as the estimated prevalence of stroke among all patients admitted to the ED with an Emergency Service dispatch of suspected stroke (∼80%)^2^ based on a 20% prevalence of stroke mimics.^18^ We calculated a minimum sample size of n=273 patients to obtain a reliable estimate of LF-MRI diagnostic performance (95% CI, 1−β=80%) and to compare with conventional neuroimaging. Referring to the evaluation of agreement between LF-MRI and conventional neuroimaging (Cohen kappa coefficient expected value=0.8, expected outcome ∼20%, 1−β=80%), we calculated a minimum sample size of n=214 patients. All our estimate take into account a rate of ∼10% patients potentially dropping out from the study. Therefore, to maximise the accuracy of our analyses, we aim to include an overall population of 100 patients for each recruiting centre (300 patients in total).

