### Study period

The start date of the study was 13 February 2023, and the expected end data is 12 February 2027. The enrolment period is 3 years, from 1 February 2024 to 31 January 2027.

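### The single agreement sample size (n=214) counts every retained patient as a scan pair, so it is not shown to cover the HF-MRI endpoint, and the passages on follow-up imaging conflict

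*Protocol article*

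**What the plan says.** - **Which scans are fixed.** Under Study design, LF-MRI is fixed by the study on admission, at 24 hours, 72 hours, discharge and 4 weeks. For the comparator, "Conventional stroke imaging will be performed as needed according to current clinical practice". The parenthesis that follows limits HF-MRI to a selection of patients. The secondary endpoint on HF-MRI (Outcomes measurement) likewise refers to routinely performed scans.
- **What the timing presupposes.** The same section also says: "At each time point, LF-MRI will be scheduled immediately after conventional neuroimaging to ensure comparability between performed investigations". The Time points and collected variables section lists conventional imaging type and findings at 24 hours, 72 hours and 4 weeks.
- **Endpoints.** Outcomes measurement sets separate agreement endpoints against CT, against HF-MRI and by stroke phase (hyperacute, 24 hours, 72 hours, 4 weeks).
- **Sample size.** There is one agreement calculation, introduced by "Referring to the evaluation of agreement between LF-MRI and conventional neuroimaging" with the inputs "Cohen kappa coefficient expected value=0.8, expected outcome ∼20%, 1−β=80"%: "we calculated a minimum sample size of n=214 patients". The only allowance for loss is about 10% dropout. Planned enrolment is 300.
- **Discharge.** Study design includes discharge among the time points for agreement. The discharge variables begin "Hospital discharge: days of hospital stay, functional outcome at discharge (modified Rankin scale), final adjudication of the event" and continue with aetiology; no imaging is listed. The phase endpoint omits discharge.
- **Dates.** "The enrolment period is 3 years, from 1 February 2024 to 31 January 2027". The expected study end is 12 February 2027.

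**The concern.** A kappa needs both scans in the same patient. Where the comparator is obtained at clinical discretion, the number of pairs is set by usual care and not by enrolment, and a dropout allowance does not cover patients who stay in the study but are never sent for that scan. For HF-MRI this follows from the article's own words: the pairs are those patients whom clinicians chose to scan. Agreement in that subset need not carry over to all suspected strokes, and its precision cannot be read from n=214.

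For follow-up, the article can be read two ways. If conventional imaging accompanies LF-MRI at each phase, the pairs exist. If it is discretionary, the later pairs may come mainly from patients with a clinical reason for a scan, and the comparator may move between CT and HF-MRI from one phase to the next. Kappas set side by side across phases would then mix lesion evolution with patient selection and change of modality. An analysis plan cannot repair this afterwards, because it cannot supply scans that were not done.

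**Working it through.** **1. Reproducing n=214.** Inputs from Sample size calculation: expected kappa k1 = 0.8, prevalence p = 0.20, power 80%, dropout 10%. From Statistical plan: alpha 0.05, taken as two-sided. The null kappa k0 is not stated; 0.6 is assumed because it returns the stated figure.

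Goodness-of-fit (Donner-Eliasziw) formula for two readings of a binary trait:

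- both positive: p² + p(1−p)k = 0.168 under k1, 0.136 under k0
- discordant: 2p(1−p)(1−k) = 0.064 under k1, 0.128 under k0
- both negative: (1−p)² + p(1−p)k = 0.768 under k1, 0.736 under k0

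S = 0.032²/0.136 + 0.064²/0.128 + 0.032²/0.736 = 0.00753 + 0.03200 + 0.00139 = 0.0409.

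n = (1.960 + 0.842)²/S = 7.849/0.0409 = 191.8, so 192 pairs. 192/0.9 = 213.3, so 214, an exact match. Some other combinations of null value and variance formula also land near 214, so k0 = 0.6 remains an inference. On this reading the dropout allowance is the only step between patients and pairs: every retained patient is a pair.

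**2. Share of patients that must be paired.** 300 × 0.9 = 270 retained. 192/270 = 71%.

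**3. Power and precision by share paired.** The documents give no HF-MRI or follow-up scan rate, so the share f is an assumed range. Pairs m = 270f. Power = Φ(√(mS) − 1.960). The 95% CI half-width for kappa is 1.96·√(0.576/m), where 0.576 is the common-correlation variance at kappa 0.8 and prevalence 0.20.

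| f (assumed) | pairs | power | half-width |
|---|---|---|---|
| 20% | 54 | 32% | 0.20 |
| 30% | 81 | 45% | 0.17 |
| 50% | 135 | 65% | 0.13 |
| 60% | 162 | 73% | 0.12 |
| 71% | 192 | 80% | 0.11 |
| 80% | 216 | 84% | 0.10 |

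**4. Sensitivity to prevalence.** In a selected subset the trait may be more common than 20%. At an assumed 50%, S = 0.05²/0.40 + 0.10²/0.20 + 0.05²/0.40 = 0.0625, so 7.849/0.0625 = 125.6, or 126 pairs. With 135 pairs, power is Φ(√(135 × 0.0625) − 1.960) = Φ(0.945) = 83%, against 65% at 20% prevalence.

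**5. Follow-up passages side by side.** The timing sentence and the list of collected variables both take a conventional scan for granted at 24 hours, 72 hours and 4 weeks. The sentence on usual care makes conventional imaging depend on need. Where no scan is needed, there is nothing for LF-MRI to follow and no finding to record.

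**6. Dates.** 31 January 2027 + 28 days = 28 February 2027, which is 16 days after 12 February 2027. Counting back, 12 February − 28 days = 15 January 2027. Enrolment from 16 to 31 January covers 16 of 1,096 days; at an even rate 300 × 16/1,096 = 4.4, about 4 patients.

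**The case against.** A reader might infer that the article claims 80% power for the HF-MRI and follow-up endpoints and that this claim fails. The documents do not support that. The sample size section ties n=214 to conventional neuroimaging as a whole and assigns it to no single modality or time point. These are secondary endpoints, which need not each be powered. The null of 0.6 and every scan share above are assumptions: 300 enrolled would be enough if about 71% of retained patients were paired, and a smaller share would do at higher prevalence. Loss of power is therefore possible but not demonstrated.

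A reader might also infer that follow-up pairs will be lost or selected. That rests on one reading of the sentence about usual care, which sits in the account of the acute work-up, beside angiography and perfusion. Two other passages point the other way, and the figure summarising study procedures is not shown. What is established is a conflict, not missing scans.

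It is also fair to say that no test of change in kappa over time is planned, that imaging type is recorded so stratification stays possible, and that much reporting detail belongs in an analysis plan. The date overrun is small, lies well inside the 10% allowance, and the end date is called expected. The discharge variables come under a list of clinical variables, and the full case report form is not shown.

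These points narrow the concern but do not remove it. HF-MRI is expressly restricted, no expected number of pairs is given for it, and the statements on follow-up imaging, discharge and dates do not fit together as written.

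**Conclusion.** The point holds in limited form.

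- **HF-MRI.** n=214 is not shown to cover this endpoint. Its pairs are a clinically selected subset by the article's own description, and the 10% dropout allowance does not account for patients never scanned.
- **Follow-up.** The statements on conventional imaging must be reconciled. Whether pairs are lost is open.
- **Size.** About 71% of retained patients must be paired for 80% power, given a null kappa of 0.6, a two-sided 5% test and 20% prevalence. Power over the assumed shares spans a range too wide to support a statement either way, and higher prevalence would raise it.
- **Hyperacute LF-MRI against conventional imaging overall.** This is not undermined, since the usual work-up there is CT and/or HF-MRI.
- **Discharge and dates.** Both are genuine inconsistencies of minor weight. The date problem touches about 4 of 300 patients if enrolment is even.

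**What to change.** 1. State which conventional scans are expected at each time point, so that the two Study design statements and the list of collected variables agree.
2. State that n=214 and 80% power refer to hyperacute LF-MRI against conventional imaging. Report HF-MRI and follow-up agreement as estimates with 95% CI, number of pairs and reason for the scan, separately for CT and HF-MRI. Make any comparison between time points within patients paired at both with the same modality.
3. Reconcile discharge imaging between Study design and the collected variables and endpoint: either record discharge findings and include them in the endpoint, or withdraw the claim of agreement at discharge.
4. Align enrolment close and study end so that the last 4-week scan falls within the study.

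The cost is protocol wording, alignment of the case report form and one date. As framed, the changes call for no added scans or patients. The downside is weaker stated support for these secondary endpoints.
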